### Timing

We estimate that both study phases can be completed in approximately 12 months.

### Data processing and analysis

Key study variables will be summarized univariately using means/standard deviations/histograms and frequencies/proportions as appropriate.

We will calculate sensitivity, specificity, positive and negative predictive values, positive and negative likelihood ratios, and the κ statistic (all with 95% confidence intervals) using standard formulas for a binomial proportion.

The mean time difference between POCUS and standard-of-care methods will be analyzed using paired sample t-tests. If the time distribution is skewed, we will examine median time differences using Wilcoxon signed-rank tests for matched data.

Data analysis will use SPSS statistical software, with the type 1 error rate set to 0.05. A subgroup analysis of premature newborns status will be performed as sample size permits. We will also analyze user accuracy as a function of number of POCUS exams performed during the study. An ad-hoc power analysis will be performed on stratified effects at study completion.

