### Sample size

Phase 1 will involve 60 healthcare providers who attend deliveries and are exclusively involved in newborn care, which include 6 neonatal attending physicians, 8 neonatal fellows, 38 postgraduate medical trainees, and 8 senior nursing staff. These providers are all skilled in standard-of-care methods for ETT confirmation. Each 2-hour training session involves 15 participants, and the sessions are conducted 4 times.

The phase 2 sample size calculation indicates that a total of 292 neonatal intubations are required. There are approximately 5000 deliveries per year at AKUH, of which approximately 12% (600) of these newborns are admitted to the NICU. Approximately 70% (420) of these patients require intubation in a given year. The rates of incorrect esophageal intubation reported in the most recent multi-center study ranged from 1 to 12% [13]. Using a conservative rate of 5%, the sample size was calculated for the primary outcome (accuracy) using a two-sided equivalence test for correlated proportions. The standard proportion of correct tracheal intubation was assumed to be 95% and the maximum allowable difference between POCUS and standard-of-care methods was set to 0.05 (*α)*. To achieve 80% power at a 5% significance level, a total of 222 participants are needed for the primary outcome.

For the secondary outcome (time difference between POCUS and standard-of-care methods), using a conservative time difference of 5 s, we estimate a total sample size of 252 newborns will be needed to achieve a two-sided alpha of 0.05 and power of 80%.

Sample size estimates for the tertiary outcome are based on the kappa (κ) statistic for measuring agreement between POCUS and standard-of-care methods. Assuming 95% true agreement and a kappa statistic of 0.90, a sample size of 292 subjects results in a two-sided 95% confidence interval with a width of 0.100 (i.e. k = 0.85–0.95) using the Cohen’s large-sample formula for standard deviation of κ.

Therefore, to achieve all study objectives, a minimum sample size of *n* = 292 will be targeted.

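### Binomial-proportion formulas are assigned to the confidence intervals of likelihood ratios and kappa, which are not binomial proportions

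*Protocol article*

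**What the plan says.** In the protocol article, Data processing and analysis names seven indices in one sentence. Four are proportions: sensitivity, specificity, PPV and NPV. The other three are "positive and negative likelihood ratios, and the κ statistic". The interval method is given once for the whole list: "all with 95% confidence intervals) using standard formulas for a binomial proportion". The article names no other interval method for the likelihood ratios or for kappa at the analysis stage.

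The Sample size section treats kappa differently. It states: "Assuming 95% true agreement and a kappa statistic of 0.90, a sample size of 292 subjects results in a two-sided 95% confidence interval" and continues "with a width of 0.100 (i.e. k = 0.85–0.95", obtained "using the Cohen’s large-sample formula for standard deviation of κ". This calculation gives the largest of the three requirements (222, 252 and 292), so it sets the target.

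On operators, the Sample size section says "Phase 1 will involve 60 healthcare providers who attend deliveries". Under Intervention – phase 1, only those who pass both examinations go on to scan in phase 2. Data processing and analysis adds: "We will also analyze user accuracy as a function of number of POCUS exams performed during the study".

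**The concern.** A binomial interval needs a count of successes out of a fixed number of independent trials. A likelihood ratio is a ratio of two proportions from different groups and runs from 0 to infinity. Kappa is corrected for chance, and its variance depends on the margins as well as on agreement. Neither is a binomial proportion, yet the word *all* puts both under the binomial rule.

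This is a stated method, not a detail left to an analysis plan. An analyst following it could not compute an interval for LR+, would get a wrong one for LR-, and, reading literally, would get one for kappa that is narrower than the precision on which the study was sized. The same formula also assumes independent scans, although the protocol foresees users scanning more than once.

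**Working it through.** **Inputs from the protocol article.** n = 292, kappa 0.90, agreement 0.95 and planned width 0.100; esophageal rate 5% ("Using a conservative rate of 5%, the sample size was calculated for the primary outcome (accuracy"), so 0.05 × 292 ≈ 15 esophageal and 277 tracheal tubes; 60 providers trained. **Assumed:** the cell counts in step 3, the 5% margins in both readings in step 2, and the intraclass correlation (ICC), equal operator loads and 20-operator case in step 5.

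**1. Reproduce the plan's kappa figure.**
- Chance agreement: pe = (po − κ)/(1 − κ) = (0.95 − 0.90)/0.10 = 0.50.
- Cohen SE = √[po(1 − po)/(n(1 − pe)²)] = √[0.0475/(292 × 0.25)] = 0.0255.
- Width = 2 × 1.96 × 0.0255 = 0.100, interval 0.850 to 0.950. Required n = 291.95, rounded up to 292. The stated figure reproduces.

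**2. Apply the analysis rule literally to kappa.**
- SE = √[0.90 × 0.10/292] = 0.0176; width 0.069, interval 0.866 to 0.934.
- Planned over literal: 0.100/0.069 ≈ 1.45.
- Sensitivity check with 5% esophageal in both readings and kappa held at 0.90: pe = 0.05² + 0.95² = 0.905 and po = 1 − 0.10 × 0.095 = 0.9905. Cohen's formula gives width 0.234 and the Fleiss-Cohen-Everitt formula 0.233. This assumes about 99% agreement, not the protocol's 95%.

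**3. Likelihood ratios, illustrative counts (tracheal = positive, 263/277 and 14/15 correct).**
- LR+ = (263/277)/(1/15) = 14.2. Then p(1 − p) = 14.24 × (1 − 14.24) = −188.6, so no binomial SE exists.
- Log method: SE = √(1/263 − 1/277 + 1/1 − 1/15) = 0.966. The 95% CI is 14.2 × exp(±1.96 × 0.966), or 2.1 to 94.6.
- LR− = (14/277)/(14/15) = 0.054. Binomial with n = 292: 0.028 to 0.080; log method: 0.032 to 0.092.
- Coding reversed (esophageal = positive): LR− = (1/15)/(263/277) = 0.070. Binomial: 0.041 to 0.100; log method: 0.011 to 0.467.

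**4. The proportions.** Binomial formulas are right in kind here. The choice among them matters in the cell of about 15. For 15/15 correct, the exact lower limit is 0.025^(1/15) = 0.78, whereas a Wald interval would have zero width.

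**5. Operator clustering.** Design effect = 1 + (m − 1) × ICC, with m the scans per operator.

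| Operators | m | ICC 0.01 | ICC 0.20 |
|---|---|---|---|
| 60 (upper bound) | 292/60 = 4.87 | 1.04 (effective n 281) | 1.77 (effective n 165) |
| 20 (assumed) | 292/20 = 14.6 | 1.14 (effective n 257) | 3.72 (effective n 78) |

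With 60 operators, intervals would be about 2% to 33% wider (√1.04 to √1.77).

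**The case against.** The strongest reply is that the sentence is loose wording with little at stake. Several parts of it stand.

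- **Kappa.** Cohen's SE is the binomial SE of observed agreement divided by (1 − pe), and the Sample size section names it. A charitable reader could take the analysis sentence to mean that formula. The text does not say so, and no such reading rescues the likelihood ratios.
- **Proportions.** A reader might infer that Wald intervals are planned and would collapse to zero width. The protocol never says Wald. Exact and Wilson intervals are also standard binomial formulas, so the sentence is correct for the four proportions. Naming the method is advice, not correction of an error.
- **Size.** A reader might infer that the kappa interval is 3.4 times too narrow (0.234/0.069). That ratio replaces the protocol's 95% agreement with 99.05%. The protocol's own planning values give about 1.45. Whether 95% agreement and kappa 0.90 can coexist at 5% prevalence is a separate question.
- **Stakes.** A reader might infer that the study's main inference fails. The primary outcome is overall accuracy, a true proportion. Likelihood ratios are not among the named outcomes, agreement is tertiary, and the failure for LR+ would be visible rather than falsely precise.
- **Clustering.** No ICC is given, the phase 2 operator count is not stated, and the effect is slight at low ICC. Planning to examine accuracy by exam count does not mean that the protocol expects it to vary. The adjustment could sit in a plan not shown. What remains is that the formula named assumes independence.

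**Conclusion.** The point holds for three of the seven indices. For a likelihood ratio above 1 the stated rule cannot be carried out, whatever the exact counts. For LR− it gives an interval, but one whose error runs from modest to large depending on which tube position is coded positive. For kappa, read literally, it conflicts with the protocol's own planning formula: width 0.069 against 0.100, about 1.45 times too narrow at kappa 0.90, 95% agreement and n = 292. If both readings had 5% esophageal tubes and kappa stayed at 0.90, the proper width would be about 0.23, but that rests on an assumption outside the protocol's kappa planning values.

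The likelihood-ratio intervals shown are illustrations from assumed counts. Clustering is a secondary point that rests on an assumed ICC and on 60 as an upper bound for operators. The primary accuracy estimate is untouched, and n = 292 was not derived from the binomial formula. The correction should be made, but it does not undermine the design.

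**What to change.** Replace the single interval rule with one for each type of index:

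- **Overall accuracy, sensitivity, specificity, PPV, NPV:** binomial intervals, preferably Clopper-Pearson or Wilson because only about 15 esophageal tubes are expected.
- **Likelihood ratios:** log-method, score or bootstrap intervals, with a stated approach for zero cells.
- **Kappa:** the large-sample standard error, consistent with the Sample size section, or a bootstrap.
- **Secondary:** also report intervals that allow for clustering by POCUS user (robust variance or a bootstrap that resamples users). This needs a user identifier for each scan, which the planned per-user analysis implies but the article does not state.

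The cost is a few sentences and minor programming, with no change to the sample size and no new measurements. The downside is somewhat wider intervals.

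### The power analysis planned on stratified effects after the study fixes no target difference; read naturally, it only restates the p-values of the exploratory subgroups

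*Protocol article*

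**What the plan says.** The relevant text closes the Data processing and analysis section of the protocol article. Two exploratory analyses come first: "A subgroup analysis of premature newborns status will be performed as sample size permits", and "We will also analyze user accuracy as a function of number of POCUS exams performed during the study". The sentence at issue follows: "An ad-hoc power analysis will be performed on stratified effects at study completion". The section runs its tests "with the type 1 error rate set to 0.05". The only tests it names are for time: "The mean time difference between POCUS and standard-of-care methods will be analyzed using paired sample t-tests", with a signed-rank alternative if times are skewed. It also plans 95% confidence intervals for sensitivity, specificity, predictive values, likelihood ratios and kappa, without saying whether these extend to subgroups.

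The Sample size section works for the whole sample only. It gives 222 for the primary outcome, 252 for the time difference, and the governing 292 for kappa: "a sample size of 292 subjects results in a two-sided 95% confidence interval with a width of 0.100". No effect, margin or size is given for any stratum.

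**The concern.** A power calculation informs a reader when the effect it refers to is chosen without sight of the results. This one is ad hoc, is done at study completion, and refers to the stratified effects, with no target difference and no stated use. The natural reading is that the effects found in the strata are fed back into a power formula. The answer is then already contained in the p-value.

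At stake is how the preterm result is read. The article's Background says the likelihood of needing intubation rises with prematurity, so whether briefly trained providers do as well in preterm newborns is a fair question. Power at the observed effect would label every non-significant subgroup result as underpowered, including one from a large stratum with a narrow interval around no difference.

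**Working it through.** **Inputs.** From the documents: type 1 error 0.05 (Data processing and analysis; two-sided for time in Sample size), target 292, a 5% esophageal rate, a 5 s time difference with n = 252 and 80% power (Sample size). Assumed: accuracy of 95% in each stratum, and a preterm share between 30% and 50%. The documents give no preterm share. The sentence at issue states no figure, so there is none to reproduce.

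**Step 1. Power at the observed effect, two-sided 5% z-test.** With z = Φ⁻¹(1 − p/2), observed power = Φ(z − 1.96) + Φ(−z − 1.96).

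- p = 0.05: z = 1.960; 0.500 + 0.000 = 50%
- p = 0.10: 38%
- p = 0.20: z = 1.282; 0.249 + 0.001 = 25%
- p = 0.50: z = 0.674; 0.099 + 0.004 = 10%
- p = 1.00: 5%

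Only p enters the formula. Every p above 0.05 gives less than about 50%, well under the 80% used in the Sample size section.

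**Step 2. Does stratum size matter?** For a two-group comparison of means with p held at 0.20, observed power is 24.9% at n = 20, 100 and 500 per group. For the paired t-test planned for time (noncentral t), p = 0.20 gives 24.3% at n = 20 and 24.9% at n = 292; p = 0.05 gives 51.1% and 50.1%. Size makes almost no difference.

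**Step 3. Contrast with an effect fixed in advance.** Taking n = 252 as a paired calculation, the implied SD of the differences is 5 × √252 / (1.960 + 0.842) ≈ 28.3 s. The article does not state this SD. With that SD and 5 s, power = Φ(5√n / 28.3 − 1.96), which is 42% at n = 100 and 70% at n = 200. This does depend on stratum size and would be informative, but the article fixes no such effect for any stratum.

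**Step 4. What intervals would show for accuracy.** Half-width for a stratum = 1.96 × √(0.95 × 0.05 / n); for the difference = 1.96 × √(0.0475/n₁ + 0.0475/n₂).

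- 50/50 (146 and 146): ±3.5 points per stratum; difference ±5.0 points
- 30/70 (88 and 204): ±4.6 points preterm, ±3.0 points term; difference ±5.4 points

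**Step 5. Esophageal tubes per stratum.** 0.05 × 146 = 7.3, so about 7 in each stratum under an even split. If all 7 are detected, the exact 95% lower limit is 0.025^(1/7) = 0.59, an interval of 59% to 100%. The accuracy half-widths in step 4 therefore say nothing reassuring about esophageal detection within a stratum.

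**The case against.** The strongest reply is that the sentence does not say the effects are the observed ones. Subgroup analysis depends on the sample size achieved, so stratum sizes are known only at completion. The authors could intend to enter design differences from the Sample size section (5 s, or 0.05) at the achieved stratum sizes. Step 3 shows that such power is not redundant. The effect to be entered is also a detail that a condensed article might leave to a fuller document. This stands in part: the observed-effect reading is an interpretation and must be stated as one. It does not clear the sentence, because those differences are set for the whole sample, nothing links them to strata, and an ad-hoc choice at completion is made with the data in view.

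Two technical points also stand. The article names no test between preterm and term newborns, so a p-value for that contrast is presumed. And the primary sample size uses an equivalence test, for which observed power is not a pure function of the p-value, although a non-significant equivalence result still returns less than 50%.

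A reader might infer that no subgroup result could ever be taken as evidence of similar performance. The documents do not support that. A power figure does not remove interval estimates, the section already plans 95% intervals for the main accuracy measures, and nothing excludes them for subgroups.

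**Conclusion.** The point holds as a limited one. On the natural reading, the planned analysis restates the p-value (50%, 25% and 10% at p = 0.05, 0.20 and 0.50) and cannot distinguish a stratum that is too small from one with no relevant difference. On the alternative reading, the effect is left open until after the data are seen. Neither serves the purpose.

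The reach is confined to exploratory subgroup results. The primary accuracy estimate, the whole-sample time comparison and the target of 292 are untouched.

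The figure of ±5.0 to ±5.4 points rests on an assumed preterm share of 30% to 50% and 95% accuracy in both strata. It applies to overall accuracy only. It would be wrong to infer from it that preterm and term newborns can be compared well on esophageal detection: about 7 such tubes per stratum under an even split, at the assumed 5% rate, cannot support that.

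**What to change.** Delete the sentence on ad-hoc power. In its place, state that accuracy, detection of esophageal tubes, detection of tracheal tubes, and the time difference between POCUS and standard of care will be reported for preterm and for term newborns with 95% confidence intervals, together with the between-stratum difference and its 95% interval, and that no power will be computed from the results. Say that esophageal detection by stratum is descriptive and will carry exact intervals.

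If the investigators do want power for a stratum, the stratum difference of interest and the expected precision at plausible stratum sizes should be written down before the data are examined.

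The cost is one sentence of protocol wording, carried into any analysis plan. It extends intervals already planned for the whole sample, drops one calculation, and changes nothing in data collection, sample size or the primary analysis.

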## Discussion

Intubation during newborn resuscitation is a critical life-saving skill that is difficult to learn and perform. Unsuccessful intubation can lead to devastating consequences, and one of the most common reasons for intubation failure of is esophageal placement of an ETT [26]. Ultrasound provides a simple, safe and effective method of differentiating between esophageal and tracheal intubations, but has not yet achieved widespread use in newborn resuscitation [27].

To our knowledge, only two previous studies have utilized ultrasound in real time for the confirmation of ETT position with comparison to standard-of-care methods [28, 29]. The first study included 16 NICU intubations and found a sensitivity of 92% and a specificity of 100% for ultrasound compared to capnography. Ultrasound was significantly slower than capnography, but significantly faster than x-ray [28]. The second study included 10 NICU intubations and 100% sensitivity and specificity for ultrasound compared to capnography, with ultrasound results generated significantly faster than x-ray [29]. Our study represents the largest study to date examining the use of POCUS for newborn intubations.

The second major strength of this study is the development and validation of a novel ultrasound simulator. Using materials costing only $2, an additional potential benefit of this study is to demonstrate that this simulator can be used to train healthcare providers in this important ultrasound skill. Simulators have the advantage of allowing providers to learn and practice skills prior to their application on patients, and other ultrasound simulators have been designed for this purpose [30]. Additional strengths of this study include 1) recorded images with quality assurance 2) different types of healthcare workers involved in being trained 3) extended follow-up period to measure skills retention, and 4) empowering health care providers to read and interpret images in real time thereby saving critical time and need for specialized human resources (radiologists).

The major limitation of this study is related to ultrasound cost as it pertains to the generalizability of the study. Although the simulator is low-cost, the ultrasound equipment is expensive and will not be able to be purchased in many low and middle-income settings at current price points. Over time, however, this will change as ultrasound technology continues to be more accessible. It is also important to note that ultrasound has a wide variety of applications in the NICU [31], and will increasingly become available for use.

## Data Availability

Given the sensitive nature of the data which includes ultrasound video clips of newborns, the data is only available to two co-authors (MT and [name]) via secured file sharing platform housed at The Hospital for Sick Children. The authors plan to publish aggregate study results in peer-reviewed journals and present the findings at conferences.

## Abbreviations

AKUH: Aga Khan University Hospital
CO2: Carbon dioxide
ETT: Endotracheal tube
LR/OR: Labour room/operating room
NICU: Neonatal intensive care unit
POCUS: Point of care ultrasound
SD: Standard deviation
